## Abstract

**Introduction:**

In rural and remote South Africa, most strokes and ischaemic heart diseases are as a consequence of hypertension, which is a modifiable risk factor. The widely recommended therapeutic approaches to control hypertension are through physical activity and diet modifications. However, there is a lack of culturally sensitive community-based, lifestyle interventions to control hypertension among rural African adult populations. We designed an intervention which recommends adjusting daily routine physical activity and dietary behaviour of adults with hypertension. This study aims to evaluate the feasibility and acceptability of HYPHEN in a rural community setting.

**Methods:**

We aim to recruit 30 adult participants with a self-report hypertension diagnosis. A one-arm, prospective design will be used to assess the feasibility and acceptability of recruitment, uptake, engagement, and completion of the 10-week intervention. Recruitment rates will be assessed at week 0. Intervention uptake, engagement, and adherence to the intervention will be assessed weekly via telephone. Blood pressure, body mass index, waist-hip ratio, urinary sodium, accelerometer-measured physical activity, and 24-h diet recall will be assessed at baseline and at 10 weeks. Qualitative semi-structured interviews will be conducted at 10 weeks to explore feasibility and acceptability.

**Discussion:**

This study offers a person-centred, sociocultural approach to hypertension control through adaptations to physical activity and dietary intake. This study will determine whether HYPHEN is feasible and acceptable and will inform changes to the protocol/focus that could be tested in a full trial.

**Trial registration number:**

PACTR202306662753321.

## Introduction

The World Health Organization projects that in the African region, by 2030, noncommunicable diseases (NCDs) will be the biggest cause of death [1]. The relative burden of NCDs is expected to increase as both HIV-/AIDS-related mortality declines with the roll-out of antiretroviral therapy and the region continues to experience the rapid urbanization of communities [2]. Hypertension, stroke, and ischaemic heart disease are among the most common NCDs causing premature deaths among adults living in South Africa [3]. Over half of strokes and ischaemic heart disease in South Africa are caused by hypertension, and these cardiovascular and cerebrovascular diseases are reported to be more prevalent in rural areas compared to urban areas [3].

The high prevalence of hypertension in South Africa will likely result in increased mortality and morbidity in rural compared to urban areas due, in part, to poorly organized health care systems, intermittent drug supply, and shortage of health care workers [4–6]. Reduced salt and caloric intake and increase in physical activity are the widely recommended therapeutic approaches to meeting national hypertension targets [7–9].

There is a paucity of research that provides a profile of daily physical activity practices of rural South African adults living with hypertension. A study by Oyeyemi and colleagues [10] assessed physical activity for rural South Africans using short versions of physical activity subjective assessment which does not provide information about the domain of physical activity (transportation, job, leisure, and housework) performed each day. Another study using a short version physical activity questionnaire by Smart Mabweazara [11] in the general population concluded that adults in rural Western Cape engaged in more physical activity than urban adults from the same province. A further study by Tomaz and colleagues [12] assessed physical activity for middle-aged and older rural adults and recommended that physical activity interventions should be targeted for adults from the age of 40 years in order to provide health benefits earlier in life.

Available literature on dietary practices of rural South African adults has provided successful intervention recommendations for hypertension, but the recommendations are not sustained in the long run. For example, a study by Charlton and colleagues [13] provided recommendations of food replacement which participants could not afford due to high unemployment rates in rural South Africa and the fact that recommended food was not part of the participants’ daily diet [14]. Another study by Najam and colleagues [15] reported that adults in rural South Africa have good nutrition knowledge, but this did not translate into regular healthy nutrition practices. The literature on physical activity and diet practices for rural South African adults points to a need to have better understanding of the sociocultural influences so that interventions targeting the control of hypertension can consider the realities of this population.

To the authors’ knowledge, there are no interventions to test whether adaptations in physical activity and diet focusing on a contextualized structured health promotion approach could lower high blood pressure in a rural South African adult population with hypertension [16, 17]. There is a need for studies to investigate the feasibility of implementing such interventions. A contextualized intervention is one that is adapted to the local context of the target population and informed by the population needs. Many adults in rural South Africa are involved in daily manual labour as part of their activities of daily living, but this is performed at low intensity and is not well documented [10]. Common manual labour activities reported by adults living in rural South Africa include walking for wood collection, different aspects of farming, yardwork, walking as a means of transport, and housework. These activities are not adequate to paint a full picture of the daily routine practices of rural adults and need further exploration [16, 18]. There is lack of information regarding the type, frequency, and intensity of physical activities performed by rural South African adults. Moreover, many diet-based interventions are usually not affordable due to high costs or not accepted by the rural adults due lack of availability and contextual considerations, hence the need for tailor-made interventions that consider the contextual realities of the population [19, 20].

We followed a systematic process to design an evidence and theory-informed contextualized 10-week physical activity and diet intervention which recommends adjusting routine physical activity and diet practices for the control of hypertension using the intervention mapping (IM) protocol [21] — HYPHEN (*HY*pertension control using *PH*ysical activity and di*E*t in a rural co*N*text). Intervention mapping is used as a planning approach to develop theory- and evidence-based health promoting intervention programmes. Intervention mapping has been suggested as a useful and effective tool to further improve the development and application of theories to promote nutrition and physical activity [22]. The tasks in the IM protocol are iterative with the programme planner revisiting previous steps throughout the process so that all objectives, outcomes, and determinants are addressed. This process allows for the development and delivery of the intervention to be replicated.

### Aim and objectives

The aim of this study is to implement and evaluate the feasibility and acceptability of a contextually appropriate educational programme for hypertension control in adults from a rural South African population.

The primary objectives of the study are as follows:To present the social and cultural beliefs, perceptions, and practices regarding physical activity and diet which influenced the development of an intervention for the control of hypertension in adults living in rural South AfricaTo implement a contextually appropriate educational intervention programme for the control of hypertension using physical activity and dietTo determine feasibility of the intervention through assessing recruitment, retention, and attrition rates, intervention uptake, engagement, adherence to the intervention, completion, and the evaluation measuresTo determine acceptability of the intervention through individual interviewsTo assess fidelity of intervention delivery using a checklist centred around the behaviour change techniques

The secondary objective of the study is as follows:To present descriptive statistics data on health-related indicators (blood pressure, physical activity, diet consumption, body mass index, urine sodium, and waist-hip ratio) before and after the intervention.

## Methods

### Study design

This feasibility study will be a one-arm community-based, prospective study. Feasibility and acceptability of recruitment, the intervention (HYPHEN), and associated outcome measures will be assessed using a mixed-method approach.

### Study site and population

This study will be conducted at Bushbuckridge subdistrict in Mpumalanga province where the Agincourt Health and Demographic Surveillance System (HDSS) has been running since 1992. The Agincourt HDSS covers an area of 450 km^2^ with 116,000 individuals (approximately 52,000 older than 18 years) living in approximately 20,000 households distributed in 31 villages [23–25]. We will sample adults aged 40 years and above within the Agincourt HDSS from the Health and Aging in Africa: A Longitudinal Study of an INDEPTH (International Network for the Demographic Evaluation of Populations and Their Health) community in South Africa (HAALSI) [26]. The prevalence of hypertension in this subdistrict for people aged 40 years and above is 57%, defined as a self-reported diagnosis of hypertension (systolic blood pressure ≥ 140 mmHg or diastolic blood pressure ≥ 90 mmHg) or self-reported taking medications for hypertension control [26].

### Sample size

A study which provides guidance on conducting feasibility studies by Tickle-Degnen [27] states that feasibility studies are not expected to have large sample sizes as they do not need to power statistical null hypothesis testing. However, Arian and colleagues [28] in their review of current best practice state that the sample size of feasibility studies should be adequate to estimate critical parameters such as recruitment rate. An overall sample size of 30 has been recommended by Lancaster, Dodd, and Williamson [29]. We will aim to recruit 30 participants at the beginning of the intervention.

### Patient identification, consent process, and ethical considerations

Eligible participants will be invited telephonically via the Agincourt HDSS from a cohort of adults with hypertension. The details of the study will be explained through a telephone call, and if the adult demonstrates interest, a household visit will be conducted to provide further information, answer any questions, and obtain written informed consent to participate. The study has received the necessary ethical clearance from the University of the Witwatersrand Human Research Ethics Committee (clearance number: M 210282) and the local Provincial Department of Health Research and Ethics Committee (clearance number: MP_202106_001). We do not anticipate any adverse events to occur because of participating in this intervention; therefore, no data monitoring committee will be required. Participants already taking antihypertensive medications will continue this treatment as usual.

#### Inclusion criteria

Ages 40 years and olderSelf-reported diagnosis of hypertension or self-reported taking medications for hypertension controlLived in the district study setting for minimum 6 months prior to start of intervention.

#### Exclusion criteria

Dependent on wheelchairs for mobility

### Preparation procedures

The primary author will train three research assistants on the entire protocol of the study including questionnaire administration, anthropometric measurements, and education of the participants. The summary of the study schedule is outlined in Table 1.

**Table 1 Tab1:** COM-B component and behaviour change techniques (BCT) used in the structured group education session targeting hypertension

Model component	Taxonomy category	BCT	Definition	Finding from needs assessment	Example
Capability	Shaping knowledge	Information about antecedents	Provide information about antecedents (e.g. social and environmental situations and events, emotions, cognitions) that reliably predict performance of the behaviour	Lack of knowledge about blood pressure and normal blood pressure values Negative influence from community resulting in myths about causes of hypertension	Knowledge about what causes hypertension and normal blood pressure values Knowledge on ways to control blood pressure such as reducing salt intake and increasing physical activity Awareness of social triggers/barriers such as cooking for the family Awareness and correction regarding common myths

### Intervention

The intervention will comprise of three components: a structured group education session, individualized physical activity education, and individualized dietary education over a period of 10 weeks (Tables 1, 2 and 3). The duration of the intervention was informed by recommendations from similar studies [30, 31]. The three components of the intervention were informed by a needs assessment from unpublished data. The first part of the needs assessment established the profile of physical activity levels of hypertensive adults in the rural subdistrict. Results found that males reported more vigorous physical activity than females at work. Females reported high frequency of moderate-intensity physical activity inside and outside the house. The second part explored the sociocultural perceptions about physical activity and dietary practices which influence behaviour change for the control of hypertension in adults from the rural subdistrict. Some key findings included a lack of variety in the daily consumed diet, and the usual diet was mainly influenced by affordability and availability. Physical activity practices were mainly influenced by community perceptions of age- and gender-related roles.

**Table 2 Tab2:** COM-B component and behaviour change techniques (BCTs) targeting individual’s physical activity behaviour

Model component	Taxonomy category	BCT	Definition	Findings from needs assessment	Example
Capability	Shaping knowledge	Instruction on how to perform a behaviour (identified by the participant) Goal setting (behaviour)	Advise or agree on how to perform the behaviour (includes ‘skills training’) Set or agree a goal defined in terms of the behaviour to be achieved	Most daily activities are performed at low intensities or in sitting positions	Changing positions (from sitting) when performing activities Increasing pace of usual active daily tasks Avoid sedentary behaviour Identifying a list of usual daily physical activities performed
Opportunity	Shaping knowledge	Instruction on how to perform a behaviour (identified by the participant)	Advise or agree on how to perform the behaviour (includes ‘skills training’)	Some daily activities performed were of moderate to high intensities	Emphasize the importance and benefits of moderate to high intensity physical activities on hypertension control
Motivation	Feedback and monitoring	Self-monitoring of behaviour	Establish a method for the person to monitor and record their behaviour(s) as part of a behaviour change strategy	Lack of motivation to maintain behaviour change recommendations	Participant to tick which activity(ies) they achieved on a weekly basis

**Table 3 Tab3:** COM-B component and behaviour change techniques (BCTs) targeting individual’s dietary behaviour change

Model component	Taxonomy category	BCT	Definition	Findings from needs assessment	Example
Capability	Shaping knowledge Antecedents	Instruction on how to perform a behaviour Avoidance/reducing exposure to cues for the behaviour Goal setting	Advise or agree on how to perform the behaviour (includes ‘Skills training’) Advise on how to avoid exposure to specific social and contextual/physical cues for the behaviour, including changing daily or weekly routines Set or agree a goal defined in terms of the behaviour to be achieved	Diet is rich in high salt content such as processed food; use of high salt spices for cooking	Education on high sodium content food items from usual diet Education on reduction in salt consumption and high salt spices Finding alternative options for food with lower sodium content (for example brown bread instead of white bread) Limiting cooking salt to one teaspoon per day
Opportunity	Shaping knowledge	Information about antecedents	Provide information about antecedents (e.g. social and environmental situations and events, emotions, cognitions) that reliably predict performance of the behaviour	Habitual consumption of self-grown vegetables and naturally growing wild herbs such as nkaka, *Aloe*, and *Moringa*)	Encourage to continue consumption of wild herbs and self-grown garden produce
Motivation	Feedback and monitoring	Self-monitoring of behaviour	Establish a method for the person to monitor and record their behaviour(s) as part of a behaviour change strategy	Lack of motivation to maintain behaviour change recommendations	Participants to tick which dietary adjustments they achieved weekly

The design of the intervention was underpinned by the COM-B model by Michie, Van Stralen, and West [32] (Fig. 1). The model identifies three factors that need to be present for any behaviour to occur — Capability, Opportunity, and Motivation. Capability is defined as the individual’s psychological and physical capability to engage in the activity concerned. The capability includes having the necessary knowledge and skills. Opportunity is defined as all the factors external to the individual and prompt or make the behaviour possible. Motivation is defined as brain processes that energize and direct behaviour, and it includes habitual processes, emotional responding, and analytical decision-making. Potential influence between components in the model can occur, for example opportunity and capability can influence motivation (Fig. 1).

**Fig. 1 Fig1:**
[figure not shown]
COM-B model of behaviour change [32]

#### Intervention component one: structured group education

Participants of the intervention will be invited to a common location in small groups (of between 6 and 10). The main focus of the group education will be to enhance capability through shaping knowledge and skills to engage in the proposed intervention. The trained research assistants will deliver the education using a printed educational pamphlet. Some topics to be covered in the discussion (informed by a contextual need assessment) will include knowledge about what causes hypertension and normal blood pressure values, knowledge on ways to control blood pressure such as reducing salt intake and increasing physical activity, awareness of social triggers/barriers such as cooking for the family, awareness, and correction regarding common myths. The group education is expected to last up to 90 min per session.

#### Intervention component two: individualized physical activity education

Participants who attended the group education session will be visited at their home by a trained research assistant to provide individual education on physical activity. Capability will be enhanced by first asking the individual to set goals by identifying the physical activities which they perform as part of their daily routine from a list (informed by a needs assessment). The research assistant will educate the participant on how to adapt performance of the physical activities. This may include changing positions (from sitting) when performing activities, increasing pace of usual active daily tasks, and avoiding sedentary behaviour. Opportunity will be enhanced by emphasizing the importance and benefits of moderate-to-high intensity physical activities on hypertension control. Participants will be motivated by weekly telephone calls where they will be asked to indicate which activities they were able to achieve that week and encouraged where they fall short. The research assistant will keep record of everyone’s weekly performance so that feedback and motivation can be enhanced during weekly telephone feedback.

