#### Intervention component three: individualized dietary education

To enhance capability, individual education on how to make dietary changes will be provided on the same visit as the physical activity education. The research assistant will provide education on food items which contains high sodium content from the participant’s usual diet, education on reduction of salt consumption and high salt spices, finding alternative options for food with lower sodium content (for example brown bread instead of white bread), limiting cooking salt to one teaspoon per day, and removing salt from the table during meals. Opportunity for consuming healthier food items will be enhanced by encouraging habitual consumption of self-grown vegetables and naturally growing wild herbs which participants already have access to in their communities. Participants will be motivated through weekly monitoring calls where they will be asked to list which dietary adjustments they achieved weekly. The research assistant will keep record of everyone’s weekly dietary habits so that feedback and motivation can be enhanced during weekly telephone feedback.

The authors are cognizance of the under-pinning theories that influence behaviour change such as the social cognitive theory [33]. The primary variable of interest in this theory of motivation is self-efficacy, which concerns someone’s belief in his/her capabilities to successfully execute necessary courses of action to satisfy situational demands [33, 34]. According to Bandura [34], a high expectation of self-efficacy and outcome expectancy leads to greater adherence to a recommended activity (in our case, physical activity and diet adaptations). Alongside the COM-B model, we developed taxonomies of behaviour change techniques (BCTs) (Tables 1, 2 and 3) to identify active intervention ingredients and allow for future replication [35, 36]. The BCTs are classified using the Behaviour Change Taxonomy [36].

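### The weekly physical activity record ticks routine activities already performed at entry and does not capture whether they were adapted, so the physical activity part of the adherence rate would not show uptake

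*Protocol article*

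**What the plan says.** **Goal setting.** In the section on individualized physical activity education, the first step is "asking the individual to set goals by identifying the physical activities which they perform as part of their daily routine from a list". Table 2 (Capability row) gives the same content: "Identifying a list of usual daily physical activities performed".

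**What is meant to change.** The next step in that section is that "The research assistant will educate the participant on how to adapt performance of the physical activities". The examples are a change of position from sitting, a faster pace and less sedentary time.

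**What is recorded each week, physical activity.** In the calls, "they will be asked to indicate which activities they were able to achieve that week". Table 2 (Motivation row) reads "Participant to tick which activity(ies) they achieved on a weekly basis".

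**What is recorded each week, diet.** In the calls, "they will be asked to list which dietary adjustments they achieved weekly". Table 3 (Motivation row) reads "Participants to tick which dietary adjustments they achieved weekly".

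**Use of the record.** The abstract says adherence is assessed weekly by telephone. Adherence belongs to primary objective (c), and an adherence rate is among the Table 4 feasibility parameters that are to inform the larger trial. The article gives no numerator, denominator or threshold for it.

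**The concern.** The item that is ticked and the behaviour the intervention tries to change are not the same thing. The listed activities are, by construction, ones the participant already does. The intervention changes how they are done. If the weekly tick shows only that an activity took place, it records the continuation of usual life.

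Adherence is one of the quantities the study is meant to estimate for a larger trial. A physical activity adherence rate that is high whether or not anyone adopted the intervention would give the planners no information on uptake, and could be taken as reassurance. The study has one arm, so no comparison group would reveal that the same ticks arise without the intervention. The problem also cannot be left to the analysis stage: if the call does not capture the adaptation, no later analysis can recover it.

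**Working it through.** The article states no adherence figure, so there is none to reproduce. The check sets the relevant passages side by side.

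| Step | Physical activity | Diet |
|---|---|---|
| Item listed at week 2 | Activity already in the daily routine (component two; Table 2, Capability) | Goals set at the visit; education starts from high-sodium items in the usual diet (component three; Table 4) |
| Intended change | Adapted performance of that activity | Less salt, substitutes, and so on |
| Item ticked weekly | Activity achieved (component two; Table 2, Motivation) | Adjustment achieved (component three; Table 3, Motivation) |
| Does the tick, as worded, require a change? | No | Yes |

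1. **Order of events.** Component two has the participant pick the activities first and teaches the adaptation afterwards. The description of week 2 agrees: education follows from the goals already set. As described, the goal item is the activity itself.

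2. **What the article ties adherence to.** The paragraph on behaviour-change theory after component three links adherence to physical activity and diet *adaptations*. The diet tick matches that. The physical activity tick does not.

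3. **Where variation is expected.** The needs assessment in Table 2 found that most daily activities are done at low intensity or sitting, and the Introduction describes manual labour as part of daily living. Whether an activity occurs is therefore the part least likely to vary. How it is done is the target, and it is not in the wording of the record.

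4. **Illustration (assumed, not from the article).** Suppose a participant lists n = 5 activities and performs all 5 each week, and k of them are done in the agreed adapted form. Suppose also that the rate is ticks divided by listed goals.

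- Recorded rate = performed / n = 5/5 = 100%, whatever k is.
- Rate for the adaptation = k / n.

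| k adapted | Recorded | Adaptation |
|---|---|---|
| 0 | 5/5 = 100% | 0/5 = 0% |
| 1 | 5/5 = 100% | 1/5 = 20% |
| 5 | 5/5 = 100% | 5/5 = 100% |

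The recorded rate is the same over the whole range from no uptake to full uptake. That follows from the wording of the tick and does not depend on choosing n = 5. The 100% does depend on the assumed scoring rule and on the participant keeping up the full routine.

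**The case against.** **The wording may already mean the adapted form.** Table 6 speaks of goals for physical activity and diet modifications, and of explaining with images how to perform them. The section on self-monitoring support says the call asks about identified goals and records progress against each participant's printed intervention. Component two speaks of participants falling short, which is the language of goal attainment. In Table 2 the list of usual activities shares a cell with changes of position and pace. These are fair points, and they show that the authors probably have the adapted form in mind. But no passage makes the tick depend on it, and the two places that describe the physical activity record name activities. Three research assistants could score the same answer differently.

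**The forms are not shown.** The printed goal sheet and call script may be more precise than a condensed article. This stands as a caution. It does not remove the point, because the article does describe the call question and the tick, and both descriptions name the wrong item.

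**Behaviour change is measured elsewhere.** Accelerometry, urinary sodium and 24-hour recall are taken at baseline and week 10, and there are exit interviews. So a reader might infer that the study cannot tell change from no change; the documents do not support that. Still, accelerometer totals do not show which agreed adaptation was made in which week, so they cannot supply the adherence rate.

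**Diet.** A reader might also infer that the diet record has the same fault, because Table 3 includes "Encourage to continue consumption of wild herbs and self-grown garden produce". That does not hold. The item sits in the Opportunity row, not with goal setting or self-monitoring, and nothing says it is ticked. The diet tick itself asks about adjustments.

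**Conclusion.** The point holds for physical activity only. As worded, the weekly physical activity record lets an unchanged routine be ticked as fully achieved, so the physical activity part of the adherence rate in primary objective (c) would not show uptake.

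The tempting stronger conclusion is that a participant who changes nothing would score as fully adherent to the whole intervention. The article does not support it, for two reasons: such a participant would have essentially no dietary adjustment to report, and no rule is stated for turning ticks into a score.

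The consequence is moderate. No go, amend or stop criterion in Table 5 uses adherence; the engagement criterion counts complete weekly data. What is affected is one descriptive rate that is meant to inform the larger trial. No size in percentage points can be derived from the article. The conclusion rests on reading the call question and the Table 2 tick literally, and would fall away if the printed form already ticks the adaptation.

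**What to change.** - **Week-2 visit:** for each listed activity, write the agreed adaptation beside it (for example, done standing or done at a faster pace) and note whether that adapted form is already practised.
- **Weekly call:** ask about and tick the adaptation, not the activity. Reword the sentence in component two and the Motivation row of Table 2 to match, so that they agree with Table 6 and with the diet record.
- **Adherence rate:** base the physical activity part on adaptations not already practised at week 2.

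The cost is one extra column on the goal sheet, one reworded question and a slightly longer week-2 visit, with no new visits or staff. The reported adherence rate will probably be lower, because it will no longer count activities that would have been done anyway.
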